## Methods: monitoring, ethics and dissemination

### Monitoring

As this study has a negligible risk classification, it does not require a data monitoring committee. The study will be monitored by an independent, certified monitor according to the Netherlands Federation of University Medical Centres guidelines for monitoring of clinical studies. The frequency and extent of study monitoring is defined in a monitor plan, which has been approved by the Board of Directors of the Radboudumc.

### Adverse event reporting

Adverse events are defined as any undesirable experience occurring to a participant during the study, whether or not related to the mindfulness intervention. All adverse events (AE) reported spontaneously by the subject or observed by the investigators during lab visits will be recorded in CastorEDC. AEs will be followed until they have ended, or until a stable situation has been reached. Depending on the event, follow up may require additional tests or medical procedures, and/or referral to the general physician or a medical specialist. Serious AEs (SAEs) will be reported during the full duration of the study, and will be reported through the web portal *ToetsingOnline* to the accredited medical ethical committee following national regulations. We will do so within 7 days of our first knowledge of SAEs that result in death, or for SAEs that are life threatening. After reporting, we will submit a preliminary report within 8 days. All other SAEs will be reported within 15 days after our first knowledge of the SAE.

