### Interventions

#### MBCT

The 8-week curriculum of the group-based intervention is in line with the MBCT program described by Segal and colleagues [19]. For the purpose of this study, the content of the self-study materials was slightly adjusted to address PD-related issues and difficulties explicitly. For example, materials specifically discuss mindful living with physical restrictions associated with PD, and describe how to deal with lifestyle changes imposed by the disease. The intervention is provided to groups of 8–10 patients, which are a combination of both MIND-PD study participants as well as people with other somatic illnesses, who are referred to the training otherwise. The MBCT consists of eight weekly sessions of 2.5 h and one 4-hour silence day between the 6th and 7th session. The sessions include meditation exercises (body scan, sitting meditation, gentle movement exercises, three-minute breathing space, daily activities with attention), psychoeducation and group discussions. Psychoeducation includes information about cognitive techniques, like monitoring and scheduling of events, as well as identification of negative automatic thoughts. In addition, all participants are encouraged to perform daily practice assignments at home for about 30–45 min per day, mainly consisting of meditation exercises. Teachers of the MBCT fulfill the advanced criteria of the Association of Mindfulness Based Teachers in the Netherlands and are registered in the Dutch register for mindfulness trainers (https://www.mindfulnessregister.nl/). These criteria are in line with the UK Mindfulness-Based Teacher Trainer Network Good Practice Guidelines for teaching mindfulness-based courses [20]. During each MBCT course, two supervision meetings are held between the mindfulness teacher(s) and the intervention supervisor (AS). In addition, two MBCT courses per teacher will be video-recorded in order to assess teacher competence and protocol adherence using the Mindfulness-Based Interventions-Teachers Assessment Criteria [21]. To monitor adherence of the participants to the intervention, the Mindfulness Adherence Questionnaire [22] will be administered during MBCT sessions 2–8, as well as every 2 months after completion of the intervention. To further encourage mindfulness adherence in the course of the follow-up period, participants will receive bi-monthly newsletters providing updates about the trial, as well as motivational videos and materials discussing mindfulness and its potential benefits. The MBCT intervention is an add-on treatment; participants remain on their usual (dopaminergic) treatment during the intervention. While participating in the study, patients are asked to refrain from starting any new treatments apart from the study intervention, unless prescribed by their doctor. Health care use in the intervention group is monitored as part of the home questionnaires at T0, T1 and T2, as well as 6 months after T0 by means of the Treatment Inventory of Costs in Patients with psychiatric disorders (TIC-P, item 1–14) [23]. At the same timepoints, relevant lifestyle factors are monitored in the home questionnaires.

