
#### CAU

Participants in the CAU arm do not receive any add-on intervention and will maintain their usual treatment. To retain commitment with the trial, and to ensure an equal amount of contact with the research personnel in both groups, participants in the CAU group will also receive bi-monthly newsletters with updates about the trial, as well as materials that provide information about PD related topics, such as gastrointestinal problems. Information in the newsletters provided to this group will not be related to mindfulness or other lifestyle interventions. Participants in the CAU arm are asked to refrain from starting any new treatments in the course of the study, unless prescribed by their doctor. Health care use is monitored by the TIC-P as described above, as well as relevant lifestyle factors.

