**MBCT arm only**										
Mindfulness adherence (MAQ)			X		X	X	X	X	X	

^1^ Primary outcome

Study timepoints are at baseline (T0) two months after baseline (T1) and 12 months after baseline (T2). HQ = home questionnaire.

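### Adverse event capture is passive and unblinded, so non-serious events are likely to be under-recorded and their counts by arm are open to ascertainment bias of unknown size and direction

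*Protocol article*

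**What the plan says.** Under Adverse event reporting the protocol article defines AEs broadly: "Adverse events are defined as any undesirable experience occurring to a participant during the study, whether or not related to the mindfulness intervention". The capture rule is narrower: "All adverse events (AE) reported spontaneously by the subject or observed by the investigators during lab visits will be recorded in CastorEDC". For serious events it adds: "Serious AEs (SAEs) will be reported during the full duration of the study".

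The rest of the schedule bears on how that rule works:

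- **Course (Interventions, MBCT).** "The MBCT consists of eight weekly sessions of 2.5 h and one 4-hour silence day between the 6th and 7th session". The adherence questionnaire (MAQ) "will be administered during MBCT sessions 2–8, as well as every 2 months after completion of the intervention". Two supervision meetings between teacher and intervention supervisor are held per course. No AE task is given to teachers or to these meetings.
- **Timing (Post-treatment assessment; Table 1).** Both arms have T1 after their cohort's course has ended. Lab visits are at T0, T1 and T2. Home questionnaires are at T0, T1, month 6 and T2 in both arms. Table 1 gives the MBCT arm the MAQ at months 4, 8 and 10 as well, when nothing else is scheduled.
- **Health care use (MBCT and CAU sections).** The TIC-P is collected in both arms at T0, T1, month 6 and T2.
- **Blinding (Randomization and blinding).** Participants know their allocation, and the coordinating researcher who acquires the data is not blinded.
- **Contact (CAU section).** Newsletters go to the control arm partly "to ensure an equal amount of contact with the research personnel in both groups".

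**The concern.** A definition that takes in any undesirable experience over 12 months is paired with a rule that waits for participants to speak up or for an investigator to notice something at a visit. Nobody is described as asking. Such a rule tends to miss non-serious events, and what it does record depends on who has occasion and reason to mention something. In an open-label trial both can differ by arm.

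At stake is how the AE table will be read. The Discussion presents MBCT as ready for broad use if effective, and participants enter with raised anxiety and depression scores (HADS total above 10). Readers will set the two columns of AE counts side by side whether or not a test is planned. An excess under MBCT could come from more occasions to report. An absence of excess could come from events in class that never reached the record.

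**Working it through.** The plan states no AE rate, capture rate or AE comparison, so there is no figure to reproduce. The check is a count of occasions, followed by a reading of the rule.

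**Exposure against observation.** Class time is 8 × 2.5 h + 4 h = 24 h, all between T0 and T1 and none of it a lab visit. The post-baseline lab visits last about 1.5 h (T1) and 4 h (T2), 5.5 h in all.

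**Gap after T1.** On the nominal schedule, 12 − 2 = 10 months without a lab visit. Baseline may fall up to 8 weeks before the course starts. T1 could then come 8 + 8 = 16 weeks after T0, about 16 × 12/52 = 3.7 months, leaving 12 − 3.7 = 8.3 months. T2 is at least 12 months after baseline, so the gap is long either way.

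**Scheduled occasions after randomization.** Group contacts are 8 sessions + 1 silence day = 9. Home questionnaires are T1, month 6 and T2 = 3. MAQ-only occasions are months 4, 8 and 10 = 3.

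| What is counted | CAU | MBCT | Ratio |
|---|---|---|---|
| Investigator lab visits | 2 | 2 | 1.0 |
| Lab visits + group contacts | 2 | 2 + 9 = 11 | 5.5 |
| Lab visits + home questionnaires + group contacts | 2 + 3 = 5 | 5 + 9 = 14 | 2.8 |
| The same + MAQ-only occasions | 5 | 14 + 3 = 17 | 3.4 |
| The same + 5 newsletters per arm (assumed number) | 10 | 22 | 2.2 |

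The ratio is 1.0 for the only contact that the capture rule names. It runs from 2.2 to 5.5 once contacts without a stated AE function are included. No single multiple describes the opportunity to report.

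**Two readings of the rule.**

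1. *The restriction to lab visits applies only to what investigators observe.* Volunteering is then open all year. The extra MBCT occasions could raise reporting in that arm, provided that contact prompts reports and that these reach the AE record. The documents do not say whether something told to a teacher does.
2. *The restriction applies to both routes.* Opportunity is then equal, but T1 and T2 are the only capture points after baseline. An event in class is recorded only if the participant brings it up unasked at a later visit.

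Reading 1 allows differential ascertainment; reading 2 means under-capture, including of events during the intervention itself. Because the two effects can pull in opposite directions, the net direction cannot be determined.

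**The case against.** Much of the case on the other side stands.

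- **Systematic data exist in both arms.** HADS, perceived stress, PDQ-39, MDS-UPDRS and TIC-P are collected on common schedules. Worsening mood, motor decline and health care use are therefore measured alike, whatever the AE log contains.
- **No between-arm harms comparison is planned** in the objectives or analyses, and the study is classed as negligible risk.
- **This is a condensed article.** The full protocol may contain elicitation wording or a route from teacher to researcher. That answers a complaint about missing detail. It does not answer the capture method that the article does state, which is spontaneous reporting plus observation at visits.

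Three stronger readings are tempting, and the documents support none of them.

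- *A reader might infer that MBCT participants have about three times the contact, so harms cannot be compared fairly.* Investigator lab visits are equal, the multiple depends on what is counted, and the extra contacts are classes and online forms with no stated AE role. The systematic measures above can still inform a statement on tolerability.
- *A reader might infer that the weekly classes contradict the CAU section's aim of equal contact.* That aim concerns research personnel, and nothing identifies the teachers as such. The MAQ-only occasions are a self-completed questionnaire on practice.
- *A reader might infer that serious events will be learned of late.* They are reported throughout the study with no difference by arm, and the month-6 questionnaire and TIC-P fall within the interval between T1 and T2.

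**Conclusion.** The point holds as a cheap improvement and is limited to non-serious AEs. As stated, the rule is likely to under-capture them, and counts by arm are open to ascertainment bias. The firm facts are 24 h of intervention outside the observation rule, a nominal 10 months without a lab visit, and an open-label design. Differential bias needs the further assumption that additional contact, or knowledge of allocation, changes what reaches the AE record. The documents give nothing from which to estimate that effect, so no size is put on it. The primary HADS analysis is not affected.

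**What to change.** Add one identically worded AE question to the home questionnaires that both arms already complete at T1, month 6 and T2. Cross-check the answers against the TIC-P entries from the same timepoints. Keep recording spontaneous reports, but base any by-arm AE summary on the solicited ones. State that events noticed by teachers in sessions go to the coordinating researcher through the existing supervision meetings, and report these separately as MBCT-arm events so that they do not enter the comparison.

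The cost is one item in three CastorEDC questionnaires and a protocol amendment, with no new visits. More minor events will need logging. Participants already past a timepoint will have only spontaneous reports for that period. At the status date of 3 June 2024, 43 of the planned 124 had been randomized and 5 had finished. At most 124 − 43 = 81 could then be covered in full and 43 − 5 = 38 in part; both figures fall as the amendment is delayed.

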### Communicating protocol amendments to relevant parties

All amendments shall be promptly communicated to the accredited medical ethical committee. Non-substantial amendments will be duly recorded and filed by the investigator without separate notification. Substantial amendments will not be implemented until approval of the accredited medical ethical committee has been obtained. Participants enrolled in the study will be informed in case there are changes or additions to the protocol, which might significantly impact their decision to continue participation. In this case, a new informed consent procedure will be initiated.

### Dissemination plans

Anonymized group-level results will be published in peer-reviewed national and international journals. Authorship of publications coming from this study will follow the research code: publications are submitted only with authors who have made a substantial contribution to the research. Statistical code used for any journal publications will be accessible online. Lay-friendly outcomes will be communicated to participants through newsletters, and with the broader patient population through the *Parkinson Vereniging* (the national patient association) and the ParkinsonNEXT platform. Professionals working with people with PD will be informed about the results of the study through ParkinsonNet, PD patient associations, presentations at national and international conferences, and via social media.

## Discussion

The MIND-PD trial is a prospective RCT investigating the short and long-term clinical and biological effects of MBCT in people with PD. The primary goal of this trial is to identify whether MBCT can effectively reduce symptoms of depression and anxiety in people with PD, as compared to care as usual. Beyond that, we aim to explore the effects of MBCT on: (a) *motor symptom severity*, (b) *stress biomarkers*, such as cortisol (in hair and saliva) and stress-related brain activity (fMRI before and after a strong stressor: socially evaluated cold pressor test), and (c) *PD progression biomarkers*, such as structural integrity of the substantia nigra and locus coeruleus (neuromelanin-sensitive MRI, diffusion MRI). Finally, we will explore the mechanisms underlying the effects of chronic and acute stress on PD symptoms (e.g. tremor, using accelerometry), by means of the clinical, neuroimaging and biochemical assessments at baseline. Insight into the mechanisms underlying stress and stress reduction in PD may pave the way to new treatment development.

MIND-PD adopts a large-scale and multidisciplinary approach, including psychological, neurological and neuroscientific assessments. Also, MBCT is a well-documented intervention, which, if proven to be effective, can be implemented readily on a broad scale. Other strengths of this trial include the large sample, statistically powered to detect a clinically meaningful difference on our primary endpoint. Also, we are the first to explore long term (> 3 months) effects of an MBI in PD, which allows us to not only identify relevant symptomatic effects of the intervention, but to begin to explore possible disease modifying effects as well [7]. Comprehensive outcome measures, including state of the art neuroimaging and markers of the biological stress response, will further provide unique insights into the cerebral and biochemical mechanisms of stress (reduction) in PD, which are unknown to date [7].

Potential challenges of this trial may be the risk of drop-out, due to the long (12 months) follow-up period. Also, participants and researchers are not blinded in the current study design, which means that we will not be able to rule out any expectation biases or observer-expectancy effects for certain assessments. In addition, including only individuals with mild-moderate symptoms of stress may limit the generalizability of our findings to the broader PD population. However, we expect this subgroup to benefit most from MBCT, thus providing insights that closely align with clinical practice. Furthermore, lifestyle changes (e.g. exercise, sleep) may occur simultaneously, or even as a result of mindfulness practice, and significant life events may come about, given the prospective nature of the trial. To account for potential effects of such changes, participants and their lifestyle will be monitored regularly. Effects of life events are equally expected in both groups, given the randomized design. Lastly, the passive control group implemented in this trial will allow us to draw excellent conclusions about the effects of stress reduction in PD, assuming that the applied intervention is successful. However, it will be difficult to differentiate specific from non-specific intervention effects, such as social support or attention, which may be larger in the MBCT condition [8]. We have carefully considered this point, and have opted for a passive instead of an active control (e.g. muscle stretching, or education about stress), because at this stage, we are specifically interested in the effects of stress reduction on PD, not so much in stress reduction by MBCT specifically. It is likely that active control interventions also influence stress levels in PD, which would in turn reduce the contrast between groups and thereby hinder possible conclusions about stress reduction in PD. Furthermore, much larger samples are necessary if an active control is used [10], which is not feasible given our comprehensive design with multiple cerebral and biochemical outcome measures.

To date, there are no known treatments to cure or effectively attenuate the progression of PD. In this trial, we investigate whether MBCT is effective in alleviating stress, and we take the first steps to explore whether a stress reducing intervention may perhaps provoke disease modifying effects. Short-term as well as long-term effects of MBCT will be measured with clinical, biochemical and neuroimaging assessments.

### Trial status

The study protocol described here has the following version numbers: Algemeen Beoordelings-en Registratieformulier number NL81309.091.22, and Commissie Mensgebonden Onderzoek Oost-Nederland (institutional review board) number 2022–15931, version 5 (January 9, 2024). The first participant for this study was included on April 17, 2023. As of June 3rd 2024, 43 participants have been randomized, 5 of these participants have finished all study procedures. Recruitment is expected to be completed by August 2025.

## Data Availability

No datasets were generated or analysed during the current study.

## Abbreviations

PD: Parkinson’s disease
RCT: Randomized controlled trial
MBCT: Mindfulness-based cognitive therapy
(f)MRI: (Functional) magnetic resonance imaging
HADS: Hospital anxiety and depression scale
MBI: Mindfulness-based intervention
CAU: Care as usual
DCCN: Donders centre for cognitive neuroimaging
Radboudumc: Radboud university medical center
MDS-UPDRS: Movement disorders society unified parkinson disease rating scale
MoCA: Montreal cognitive assessment
PSS: Perceived stress scale
PSQ-39: Parkinson’s disease questionnaire 39
PASS: Positive appraisal scale
RRS: Ruminative response scale
FFMQ: Five facet mindfulness questionnaire
GSES: General self-efficacy scale
SCS-SF: Self-compassion scale-short form
MAQ: Mindfulness adherence questionnaire
SECPT: Socially evaluated cold pressor task
RLD: Radboudumc laboratory for diagnostics
hsCRP: High sensitive c-reactive protein
TR: Repetition time
TE: Echo time
FA: Flip angle
TI: Inversion time
FOV: Field of view
LMM: Linear mixed model
FSL: FMRIB software library
SPM: Statistical parametric mapping
ICA: Independent component analysis
AE: Adverse event
SAE: Serious adverse event
